### Sample size

The TASTE trial sample size of 330 infants had 90% power to detect a difference of 0.21 weight *z*-scores at discharge, considering multiples from one pregnancy as a cluster for a 2-sided alternative hypothesis using a generalized estimating equations model. In the TASTE trial, a total of 334 infants were discharged from the hospital and assessed for the primary outcome; however, only 270 of these were eligible for routine clinical follow-up at 2 years CA (< 28 weeks postmenstrual age and/or < 1000 g birth weight). Assuming a similar follow-up rate of 90% to that seen in cohorts at 2 years CA from the Australian state of Victoria, this follow-up study was thus expecting 243 participants. Assuming the same cluster size as for the original study, 1.09, and an intra-cluster correlation of 0.69 (based on that for weight *z*-score at discharge), we have more than 80% power to detect a difference of 13.7% (87.7% smell and taste group, 74% routine care group) at a significance level of 0.05 in the primary outcome of this follow-up study (survival free of moderate or severe neurodevelopmental impairment at 2 years CA) using a logistic generalized estimating equations analysis. A difference of 13.7% would, however, be considered larger than a minimum clinically significant effect but this sample size is not large enough to detect smaller differences reliably [27]. This trial's outcome data could potentially be used in meta-analyses of trials with similar interventions and outcomes, as well as informing the development of future studies.

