### Statistical methods

Statistical analysis will be performed by the authors [name] and [name] with the assistance of other study group members. Data will be exported from an Excel spreadsheet to a statistical package for analysis (Stata 17; College Station, Texas, USA). Data will be analyzed on an intention-to-treat basis. All randomized infants will be included in the primary analysis unless consent has been withdrawn.

There will likely be some substantial missing data as this is a follow-up study. Initially, patterns of missingness of data will be assessed and this information used to determine if missingness is likely to be completely at random (MCAR; missingness is unrelated to values of any known or unknown variable), at random (MAR; missingness of a variable’s values is dependent on known variables other than itself), and not at random (MNAR; missingness depends on the value of the missing value). We plan to use multiple imputation (mi suite of commands in Stata) to impute missing data and jointly analyze the multiple imputed datasets. These methods assume a MAR mechanism of missingness. In practice, it is difficult to definitively show that a variable is MAR rather than MNAR. As such, sensitivity analyses will be performed to see how specific violations of this assumption affect the outcome.

The primary outcome, survival free of moderate or severe neurodevelopmental impairment, and other outcomes with categorical data will be analyzed using a logistic generalized estimating equations analysis (xtlogit Stata command) and subgroup analyses of the primary outcome will be undertaken within each stratum of the stratifying variables (sex, postmenstrual age at birth, birth hospital). Univariate and where appropriate multivariate generalized estimating equations analyses will be used for continuous secondary outcome measures (xtgee command). All outcomes will be assessed against an alternative hypothesis of superiority.

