## Discussion

This neurodevelopmental follow-up study was affected by the COVID-19 pandemic. Melbourne was in prolonged lockdown while Brisbane was affected by extensive travel restrictions and several shorter regional lockdowns. Neurodevelopmental follow-up clinics were never closed, but some study families were unable to travel the required distances, did not attend hospital appointments to avoid potential exposure to COVID-19, or were otherwise affected by the COVID-19 pandemic [28]. These extenuating circumstances impacted this 2-year follow-up study.

During the COVID-19 pandemic, some clinical trials were paused to manage the public health crisis. This follow-up study was embedded into the routine neonatal follow-up program of the respective hospital. Follow-up assessments were not interrupted by public health measures at the Mater Mothers’ Hospital in Brisbane, but at the Royal Women’s Hospital in Melbourne, several prolonged lockdowns made it impossible for trial participants to attend outpatient appointments, or outpatient follow-up was canceled. Therefore, this follow-up study will have missing data, leading to a reduction of statistical power to detect a clinically important difference between groups.

Enrollment of a smaller proportion than planned may result in bias, thus compromising the generalizability of the results. Loss of power will be evaluated and discussed in the final report of the follow-up study. In addition, a table comparing study participants with complete data and those without complete data, stratified by the intervention, will be presented. Regardless of the likely presence of attrition bias, the TASTE trial presents a unique opportunity to obtain longer-term outcomes and may inform the design of future trials.

If missingness of follow-up data is plausibly viewed as *missing completely at random*, meaning that the missingness is independent of any measured or unmeasured participant characteristic, attrition bias is unlikely. If missingness is likely *missing at random*, an appropriate statistical analysis method to control for potential bias, such as inverse-probability weighting or multiple imputations, will be applied. If the missingness is plausibly not missing at random, a definitive bias adjustment may not be possible, and researchers will consider using appropriate sensitivity analysis methods [29].

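### The stated power of more than 80% does not follow from 243 participants: with a two-sided 5% test the protocol's own inputs give about 73–76%

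*Protocol article*

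**What the plan says.** The Sample size section of the protocol article builds its power statement in three steps.

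- **Numbers.** Of the 334 infants discharged, "only 270 of these were eligible for routine clinical follow-up at 2 years CA". "Assuming a similar follow-up rate of 90% to that seen in cohorts at 2 years CA", the section concludes that "this follow-up study was thus expecting 243 participants".
- **Clustering.** "Assuming the same cluster size as for the original study, 1.09", and an intra-cluster correlation of 0.69 borrowed from the discharge weight *z*-score.
- **Claim.** "we have more than 80% power to detect a difference of 13.7% (87.7% smell and taste group, 74% routine care group"). The analysis named is logistic generalized estimating equations (GEE), with alpha set to 0.05.

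No sidedness is given for this calculation. The same section describes the parent trial's calculation as two-sided. Statistical methods adds only this: "All outcomes will be assessed against an alternative hypothesis of superiority". The Discussion expects pandemic losses on top: "this follow-up study will have missing data, leading to a reduction of statistical power to detect a clinically important difference between groups".

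**The concern.** The sentence gives every input needed to check it except sidedness. On an ordinary two-sided reading, a 13.7-point difference around these rates, with about 120 infants per arm, looks short of 80% power.

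This is the article's only power statement for the primary outcome of the follow-up. If it is too high, a null result would be read against a type II error risk of under 20% when the design inputs imply about 24% to 27%. The Discussion also promises to evaluate loss of power in the final report, and that evaluation would start from a baseline that is too favourable. The protocol already regards 13.7 points as exceeding the smallest effect that would matter clinically, and the difference actually detectable at 80% power is larger still.

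**Working it through.** **Inputs** (all from Sample size): N = 243 = 0.90 × 270; p1 = 0.877, p2 = 0.74, difference 0.137; mean cluster size 1.09; intra-cluster correlation 0.69; alpha 0.05. Equal arms are assumed (the parent trial randomized 196 and 200). The test is taken as two-sided, so z = 1.96.

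**Effective sample size.** Design effect = 1 + (1.09 − 1) × 0.69 = 1.0621. Effective N = 243 / 1.0621 = 228.8, or n = 114.4 per arm.

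**Trying to reproduce the stated figure.** The binomial variances are 0.877 × 0.123 = 0.1079 and 0.74 × 0.26 = 0.1924.

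- *Unpooled:* SE = √((0.1079 + 0.1924) / 114.4) = 0.0512; 0.137 / 0.0512 = 2.67; 2.67 − 1.96 = 0.71; power 76.2%. The arcsine formula also gives 76.2%.
- *Pooled:* mean proportion 0.8085; null SE = √(2 × 0.8085 × 0.1915 / 114.4) = 0.0520; (0.137 − 1.96 × 0.0520) / 0.0512 = 0.68; power 75.3%.
- *Log-odds Wald, the scale of the planned logistic analysis:* log odds ratio 0.918; SE = √(1/(114.4 × 0.1079) + 1/(114.4 × 0.1924)) = 0.356; 0.918 / 0.356 − 1.96 = 0.62; power 73.3%. A simulation of a cluster-robust logistic analysis (20,000 runs) gives 73.4%.

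None reproduces more than 80%.

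**Variants**

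| Reading | Pooled | Unpooled | Log-odds |
|---|---|---|---|
| N = 243, two-sided, clustered | 75.3% | 76.2% | 73.3% |
| N = 243, two-sided, clustering ignored | 77.8% | 78.7% | 75.9% |
| N = 243 read as clusters, two-sided | 78.9% | 79.7% | 76.9% |
| N = 270, two-sided, clustered | 79.6% | 80.5% | 77.7% |
| N = 243, one-sided 5%, clustered | 84.2% | 84.8% | 82.6% |

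A continuity correction lowers the two-sided figure at 243 to 69.6%, and the one-sided figure to 79.8%.

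**Analysed N needed for 80%** (two-sided, design effect 1.0621): 267 unpooled, 273 pooled, 286 log-odds.

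**Difference detectable with 80% power from a 74% control rate**

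| Reading | Unpooled | Pooled | Log-odds |
|---|---|---|---|
| N = 243, two-sided | 14.3 | 14.4 | 14.8 |
| N = 270, two-sided | 13.6 | 13.8 | 14.1 |
| N = 243, one-sided 5% | 12.9 | 13.0 | 13.2 |

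(percentage points). The stated 13.7 lies between the two-proportion results for 270 infants, two-sided. It fits neither row for 243.

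**The case against.** The strongest reply is that the sentence does not state sidedness. The two-sided wording belongs to the parent trial's calculation for a different outcome, and Statistical methods speaks only of superiority. A one-sided 5% test with 243 infants gives 82.6% to 84.8%, so the claim would then be true. What stands is that the shortfall depends on a two-sided test. But two-sided is the only sidedness the article states. Superiority does not imply a one-sided test: Study design also calls the parent trial a superiority trial, and that trial was powered two-sided. A one-sided calculation would also have led to a difference of about 12.9 to 13.2 points, not 13.7. If a one-sided test was meant, the text has to say so.

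A reader might infer that the power was computed on all 270 infants with the 10% loss forgotten, or that 80% is reached only with all 270. The article does not support either as fact. With 270 infants, power is 80.5% unpooled but 79.6% pooled and 77.7% on the log-odds scale, and the number needed runs from 267 to 286. The match to 270 is suggestive and no more.

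It is also fair to say that the practical weight is limited. The sample was set by eligibility for routine follow-up rather than by this calculation, follow-up closed in October 2022, and a null result should be read mainly from its confidence interval. The article already admits that smaller differences cannot be detected reliably and that missing data will cost power. These points limit the consequence but do not correct the figure: the article still asserts more than 80% for 13.7 points, and it presents the pandemic losses as a reduction from there.

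**Conclusion.** The point holds. With 243 participants, 1:1 allocation, a design effect of 1.0621 and a two-sided 5% test, power for 74% versus 87.7% is about 73% to 76%, some 4 to 7 points below the 80% the protocol says is exceeded. The conclusion does not depend on the formula or on the clustering assumption: with clustering ignored, power is still at most 78.7%. It does depend on the test being two-sided, which is the natural reading but is not written for this calculation. That the 10% loss was left out is a possible explanation, not an established one. The error affects how the result is interpreted, not how the study was conducted or will be analysed.

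**What to change.** In Sample size, state that the test is two-sided and replace the power claim with wording such as: *With 243 participants, a design effect of 1.06 and a two-sided significance level of 0.05, there is about 75% power (73–76% by method) to detect 74% versus 87.7%, or 80% power for a difference of about 14.3–14.8 percentage points.* The loss-of-power evaluation promised in the Discussion should take this as its baseline.

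The cost is a sentence or two of text and a slightly less favourable stated power. Enrolment, outcome definitions and analysis are unchanged.

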### Recruitment

Clinical staff routinely cross-checked medical records for possible deaths before inviting a family to a routine follow-up appointment.

### Allocation

This is the follow-up study for the TASTE trial. The original TASTE trial was open-label, whereas the outcome assessors in the current follow-up study were blind to the intervention. Details regarding the trial conduct auditing, sequence generation, allocation concealment mechanisms, implementation, and discussion of the absence of blinding the intervention are available in the TASTE trial protocol and publication [19, 23].

### Data management

Parents specifically consented to data collection of the current follow-up when they consented to the original TASTE trial. This follow-up study did not involve the collection of biological specimens for storage. Data were sourced from clinical care team notes, medical records, and from parents directly. Each infant has been assigned a study number when recruited to the TASTE trial and data were collected under that study number. Individual participant identifiers apart from study numbers were removed when data were entered onto a paper case record form, then transferred by the data manager to an Excel spreadsheet and stored on a password-protected computer on the Mater Mothers’ Hospital’s computer network. Each data set will be checked by the principal investigator for plausibility and data range checks are applied in the database where appropriate. A data-sharing agreement has been established between the two participating hospitals, and all study group members have access to the final data set.

### Statistical methods

Statistical analysis will be performed by the authors [name] and [name] with the assistance of other study group members. Data will be exported from an Excel spreadsheet to a statistical package for analysis (Stata 17; College Station, Texas, USA). Data will be analyzed on an intention-to-treat basis. All randomized infants will be included in the primary analysis unless consent has been withdrawn.

There will likely be some substantial missing data as this is a follow-up study. Initially, patterns of missingness of data will be assessed and this information used to determine if missingness is likely to be completely at random (MCAR; missingness is unrelated to values of any known or unknown variable), at random (MAR; missingness of a variable’s values is dependent on known variables other than itself), and not at random (MNAR; missingness depends on the value of the missing value). We plan to use multiple imputation (mi suite of commands in Stata) to impute missing data and jointly analyze the multiple imputed datasets. These methods assume a MAR mechanism of missingness. In practice, it is difficult to definitively show that a variable is MAR rather than MNAR. As such, sensitivity analyses will be performed to see how specific violations of this assumption affect the outcome.

The primary outcome, survival free of moderate or severe neurodevelopmental impairment, and other outcomes with categorical data will be analyzed using a logistic generalized estimating equations analysis (xtlogit Stata command) and subgroup analyses of the primary outcome will be undertaken within each stratum of the stratifying variables (sex, postmenstrual age at birth, birth hospital). Univariate and where appropriate multivariate generalized estimating equations analyses will be used for continuous secondary outcome measures (xtgee command). All outcomes will be assessed against an alternative hypothesis of superiority.

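### Three sections give incompatible rules for missing primary-outcome data, so the primary analysis is not uniquely fixed

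*Protocol article*

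**What the plan says.** Three sections of the protocol article bear on missing primary-outcome data.

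- **Methods, Outcomes.** An infant with one or more primary-outcome components missing, and no disability on the components that are present, is left out of the primary outcome analysis.
- **Methods, Statistical methods.** All randomized infants enter the primary analysis unless consent was withdrawn. As a first step, "patterns of missingness of data will be assessed and this information used to determine if missingness is likely to be completely at random", or at random, or not at random. The section then states: "We plan to use multiple imputation (mi suite of commands in Stata) to impute missing data and jointly analyze the multiple imputed datasets". It notes that this assumes MAR, concedes that "In practice, it is difficult to definitively show that a variable is MAR rather than MNAR", and commits that "sensitivity analyses will be performed to see how specific violations of this assumption affect the outcome".
- **Discussion.** Handling follows the judged mechanism. Under MCAR, attrition bias is called unlikely and no method is named. Under MAR, "an appropriate statistical analysis method to control for potential bias, such as inverse-probability weighting or multiple imputations, will be applied". Under MNAR, "researchers will consider using appropriate sensitivity analysis methods".

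Study design says that this follow-up protocol exists partly to set out the statistical analysis and to allow for COVID-19, which the parent protocol did not do. Follow-up ended in October 2022, and the analyses are described in the future tense.

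**The concern.** A statistician following the Outcomes section would drop undetermined infants. One following Statistical methods would impute them. One following the Discussion would first decide on a mechanism and then choose. These are different primary analyses of the same endpoint.

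The mechanism step cannot settle the matter. Observed patterns can show that missingness is related to measured variables, which is evidence against MCAR. They cannot tell MAR from MNAR, because the values that would decide it are the missing ones.

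Two things are at stake. The estimate may depend on which rule is followed. The choice may also be made once the data are in hand: assessments are finished, the authors do the analysis, and Data management gives all study group members access to the final data set.

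**Working it through.** **1. The rules side by side**

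| Question | Outcomes | Statistical methods | Discussion |
|---|---|---|---|
| Infant with undetermined status | Excluded | Included, imputed | Depends on judged mechanism |
| Method | Complete cases | Multiple imputation under MAR | MCAR: none named; MAR: weighting or imputation; MNAR: no definitive adjustment may be possible |
| Sensitivity analysis | Not mentioned | Will be done | Only considered, and only under MNAR |

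The first two columns contradict each other outright. The third loosens both commitments of the second: imputation becomes one of two examples in one branch, and sensitivity analysis becomes optional.

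**2. Is an MCAR branch tenable?**

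Statistical methods defines MCAR as missingness unrelated to any known or unknown variable. Two facts in the article count against it:

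- Hospital: public health measures did not interrupt assessments in Brisbane, while Melbourne lost appointments to lockdowns (Discussion).
- Gestation and birth weight: routine follow-up was limited to infants under 28 weeks and/or under 1000 g (Eligibility). Of 334 discharged infants 270 qualified (Sample size), so 334 − 270 = 64, or 64/334 = 19.2%, fell outside it because of measured characteristics.

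The Discussion itself expects attrition bias.

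**3. How much is missing?**

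The plan's own figure reproduces: 270 × 0.90 = 243. With 243 assessed, the share without an assessment is:

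- of 270 eligible: 1 − 243/270 = 10.0%
- of 334 discharged: 1 − 243/334 = 27.2%
- of 396 randomized: 1 − 243/396 = 38.6%, an upper figure because deaths are known outcomes

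Actual follow-up is not stated.

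**4. Room for the handling rule to matter**

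Assume that the planning rates (87.7% and 74%) hold among those seen and that a fraction f is seen in each arm. The complete-case difference is then 13.7 points. Any imputation must fall between 0.877f − [0.74f + (1 − f)] and [0.877f + (1 − f)] − 0.74f.

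- f = 0.90: 0.7893 − 0.7660 = +2.3 points, to 0.8893 − 0.6660 = +22.3 points
- f = 0.80 (assumed): 0.7016 − 0.7920 = −9.0 points, to 0.9016 − 0.5920 = +31.0 points

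These are logical limits, not expected differences.

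**5. An illustration of two rules disagreeing under MAR (all inputs assumed)**

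There is no treatment effect. Half the infants are in each of two gestation groups, with survival free of impairment 88% and 72%, so 80% in both arms. Infants are split equally between hospitals, which lose 5% and 20%. In the intervention arm only, the lower-gestation group loses a further 20 points.

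- Retention is 1 − (0.05 + 0.20)/2 = 0.875, and 0.675 in the group with extra loss.
- Complete-case, intervention: (0.88 × 0.875 + 0.72 × 0.675)/(0.875 + 0.675) = 1.256/1.55 = 81.0%.
- Complete-case, control: 80.0%.
- Complete-case difference: +1.0 point against a true value of 0. Weighting by the inverse retention probability restores 0.

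If loss were the same in both arms, the gap in this example would vanish.

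**6. Cost of an open choice**

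If the more favorable of two 5% two-sided tests were reported, simulation gives a type I error of 7.8%, 7.0% and 6.5% for correlations of 0.80, 0.90 and 0.95 between the two test statistics (assumed values).

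**The case against.** The strongest reply is that Statistical methods, the operative section, already does most of what is needed. It plans imputation without making it conditional, states the assumption, admits that MAR and MNAR are hard to tell apart, and commits to sensitivity analyses. The sentence on patterns does not say that the judgment selects the primary analysis. On this view the Discussion is only loose commentary, and detail belongs in an analysis plan that is not shown.

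Much of this stands, and it rules out several stronger readings that a reader might infer:

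- *That no method is planned.* Imputation is named.
- *That the primary analysis will be picked afterwards among complete-case, weighting and imputation.* The Discussion never names a complete-case analysis; at most its MCAR branch implies one. Complete-case handling appears under Outcomes as a fixed rule, so that part is a contradiction between sections and not a deferred choice. Nothing in the article says that anyone had seen results by arm.
- *That the defect can be sized as share missing times departure from MAR.* That product is MNAR bias, which imputation under MAR would share. It does not measure the inconsistency.
- *That the clinic statements decide the matter.* The Discussion says "Neurodevelopmental follow-up clinics were never closed" and, of Melbourne, "or outpatient follow-up was canceled". The wording is loose, but a service can stay open while appointments fall through at one site, and neither statement fixes the method.

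What does not stand is the appeal to another document. This is not an omission: three stated rules conflict, in an article that says it is there to define the analysis. Nor can the exclusion under Outcomes be confined to secondary outcomes or to a supportive analysis, because it is worded for the primary outcome analysis.

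**Conclusion.** The concern holds as an inconsistency that should be resolved. Outcomes, Statistical methods and Discussion do not lead to one primary analysis. The mechanism judgment in the Discussion cannot choose between MAR and MNAR, and its MCAR branch conflicts with the article's own account of who was lost.

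The size can only be bracketed. The share without an assessment runs from 10% to at most 39% depending on the denominator, if 243 infants were assessed. The logical limits on the difference at 90% follow-up are wide (+2.3 to +22.3 points), but the one worked comparison of rules under MAR gives about 1 point, and only because loss was assumed to differ by arm. The article gives no arm-related cause of loss. The inflation to 6.5% to 7.8% applies only if the better of two results were reported, which the article does not suggest anyone intends.

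**What to change.** Reconcile the three sections to one rule, fixed before outcomes are examined by arm:

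1. Primary: multiple imputation under MAR, as Statistical methods already plans, whatever pattern of missingness is seen.
2. Supportive: the complete-case analysis now under Outcomes, and inverse-probability weighting, both labeled as such.
3. Always run a sensitivity analysis for MNAR, for example delta-adjusted imputation. The delta values can be left to the analysis plan.
4. Keep tables of missingness patterns, including the planned comparison of infants with and without complete data, as description only. Remove the branching by mechanism from the Discussion.

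The cost is mainly wording in three places. The imputation software is already planned; the delta adjustment adds one loop to it and the weighting adds one model. No further data collection is needed.

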### Outcomes

The primary outcome is survival free of moderate or severe neurodevelopmental impairment. The primary outcome will also be assessed within each stratifying variable: postmenstrual age at birth (< 27 or ≥ 27 weeks), sex, and study hospital. Moderate disability comprises moderate neurodevelopmental delay (Bayley-III/Bayley-4 cognitive, motor, and/or language composite scores < -2 to -3 SDs) or moderate cerebral palsy (walking at 2 years with the need for an assistive technology device, GMFCS level II or III). Severe disability comprises severe neurodevelopmental delay (Bayley-III/Bayley-4 cognitive, motor, and/or language composite scores < -3 SDs) or severe cerebral palsy (not walking at 2 years and not expected to walk, GMFCS level IV and V), blindness, or deafness. Participants for whom disability status cannot be determined (i.e., those with missing data for one or more primary outcome components and no disability on the non-missing components) will be excluded from the primary outcome analysis.

Secondary outcomes include:Death before 2 years of ageRate of mild, moderate, and severe disability. Mild disability comprises mild neurodevelopmental delay (Bayley-III/Bayley-4 cognitive, motor, and/or language composite scores < -1 to -2 SD) or mild cerebral palsy (walking at 2 years without limitations but signs of cerebral palsy, GMFCS I)Mild, moderate, and severe cerebral palsy (GMFCS)Mild, moderate, and severe neurodevelopmental delay (Bayley-III/Bayley-4)Centiles of the Bayley-III/Bayley-4 cognitive, language, and motor composite scoresHead circumference, weight, length, and respective *z*-scores at 2 years of agePartial or exclusive breastfeeding and/or presence of a nasogastric tube or percutaneous endoscopic gastrostomy feeding at 3, 6, and 12 monthsRespiratory support at 2 years of ageOral feeding at 2 years of age

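### Subgroup effects are specified only as separate within-stratum analyses, with no interaction test named; at the planned effect, equal in both strata, one-stratum-only significance would occur about half the time per variable

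*Protocol article*

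**What the plan says.** The subgroup method appears twice in the protocol article. Under Outcomes: "The primary outcome will also be assessed within each stratifying variable", followed by three two-level variables, namely postmenstrual age at birth (below 27 weeks, or 27 weeks and above), sex, and *study hospital*. Under Statistical methods: "subgroup analyses of the primary outcome will be undertaken within each stratum of the stratifying variables (sex, postmenstrual age at birth, birth hospital"). That section also says that every outcome is assessed against a superiority alternative. Neither section names a treatment-by-subgroup interaction, and neither says how results in different strata are to be compared or interpreted. Stratum sizes are not given. The third variable is *study hospital* in one section and *birth hospital* in the other.

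The Sample size section supplies the figures needed to judge the consequences: "this follow-up study was thus expecting 243 participants", and "we have more than 80% power to detect a difference of 13.7" percentage points, that is, 87.7% with smell and taste against 74% with routine care.

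**The concern.** A subgroup analysis is done to learn whether the effect differs between subgroups. A result within boys and another within girls do not answer that, because a significant result beside a non-significant one is not evidence of a difference. With the sample cut in two, each stratum is badly underpowered, so discordance arises often by chance alone. A reader who sees benefit in one stratum and none in the other may take it for effect modification by sex, maturity or hospital.

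The hospital comparison is the most exposed. The Discussion reports that follow-up assessments in Brisbane were not interrupted by public health measures, while Melbourne lockdowns prevented attendance or led to cancellations. The two strata may therefore carry unequal information for reasons unrelated to the intervention. The primary analysis is not affected; what is at stake is the subgroup claims in the final report.

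**Working it through.** **Inputs (Sample size section unless noted).**
- Eligible: "only 270 of these were eligible for routine clinical follow-up at 2 years CA". Follow-up 90%, so 270 × 0.90 = 243.
- Rates: "a difference of 13.7% (87.7% smell and taste group, 74% routine care group").
- Cluster size 1.09 and intra-cluster correlation 0.69, so design effect = 1 + (1.09 − 1) × 0.69 = 1.0621.
- Significance level 0.05. The follow-up power statement gives no side; two-sided is assumed, as in the parent trial.
- Allocation 196:200 (Study design), taken as 1:1.
- Stratum shares are not given; 50/50, 60/40 and 70/30 are assumed. Both strata are assumed to have the same rates.

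**The plan's own power figure.** Effective N = 243 / 1.0621 = 228.8, or 114.4 per arm. With n per arm and p̄ the mean of the two rates,

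power = Φ{ [d√n − 1.96√(2p̄(1−p̄))] / √(p₁(1−p₁) + p₂(1−p₂)) }.

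This gives 75.3% two-sided (76.2% with unpooled variance) and 84.2% one-sided. The stated figure of more than 80% is thus not reproduced two-sided at 243. That is a separate matter, and the last check below shows that the present point does not depend on it.

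**Power in a half-sample stratum.** n per arm = 228.8 / 4 = 57.2, and p̄ = 0.8085.
- d√n = 0.137 × √57.2 = 1.036
- 1.96 × √(2 × 0.8085 × 0.1915) = 1.091
- √(0.877 × 0.123 + 0.74 × 0.26) = √0.3003 = 0.548
- power = Φ[(1.036 − 1.091) / 0.548] = Φ(−0.10) = 46.0% (47.2% unpooled)

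**Chance that exactly one of two strata is significant, same true effect in both.** With stratum powers a and b this is a(1 − b) + b(1 − a).

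| Split | a | b | Exactly one significant |
|---|---|---|---|
| 50/50 | 46.0% | 46.0% | 49.7% |
| 60/40 | 53.2% | 38.2% | 50.8% |
| 70/30 | 59.8% | 30.0% | 53.9% |

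At 50/50, both strata are significant 21.2% of the time and neither 29.1%.

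**Smaller identical effects, from 74%, equal strata.**

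| True difference | Power per stratum | Exactly one significant |
|---|---|---|
| 10 points | 25.7% | 38.2% |
| 7 points | 14.3% | 24.5% |
| 5 points | 9.1% | 16.6% |
| 0 | 5% | 2 × 0.05 × 0.95 = 9.5% |

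**Three variables together.** In a simulation of 6,000 trials at the planned effect, with the three variables generated independently, at least one of the three pairs was discordant in about 74% (all 50/50) to 78% (50/50, 60/40 and 70/30).

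**The alternative.** In the same simulations, which compared risk differences between strata, an interaction test at 0.05 signalled a difference in 4.9% to 6.0% of trials per variable when the effect was identical. Its power for 13.7 points in one half and none in the other: variance = 0.3003 / 57.2 + 2 × 0.74 × 0.26 / 57.2 = 0.00525 + 0.00673, so SE = 0.1094 and power = Φ(0.137 / 0.1094 − 1.96) = Φ(−0.71) = about 24%.

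**Sensitivity at the planned effect.** If overall power is taken as 80%, half-sample power is 50.8% and discordance 50.0% (54.9% at 70/30). One-sided tests at 50/50 give 48.5%. Follow-up of 60% to 80% instead of 90% gives 44% to 52% for splits of 50/50 and 70/30.

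**The case against.** The strongest reply is that the article is silent on an interaction test and does not exclude one; an analysis plan that is not shown may contain it. Within-stratum estimates are also legitimate, and the fix below keeps them. A reader might infer that the authors have ruled out an interaction test, or intend to compare strata by significance. The text supports neither: it gives no rule for comparing strata, and the superiority sentence implies only that outcomes are tested. Something of the point survives, however. The Study design section presents this protocol as the place where the follow-up analysis is defined, and the one subgroup method it states does not address whether effects differ.

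A reader might also infer that discordance is as likely as not whatever the true effect. It is not. The 50% figure belongs to the planned 13.7 points, which the Sample size section itself calls larger than a minimum clinically significant effect. At smaller effects the figure falls as tabulated above.

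It can fairly be added that the interaction test would seldom detect real effect modification here. That stands. It limits false claims of a difference and does little more.

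Finally, the two hospital terms might be taken to mean that the subgroup is not the randomization stratum. Both sections call it a stratifying variable, and the article reports no infants born elsewhere and transferred in, so this is only a wording conflict of unknown practical size.

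**Conclusion.** The point holds in this limited form. The article specifies subgroup analyses of the primary outcome only within strata and names no interaction test, and within-stratum results do not test whether the effect differs. At the planned effect, identical in both strata, significance in one stratum only has a probability of about 50% to 54% per variable, against about 5% false signals from an interaction test. At 10, 7, 5 and 0 points the probability is about 38%, 25%, 17% and 10%. These figures rest on assumed splits between 50/50 and 70/30, the same rates in both strata, two-sided 0.05, the stated design effect and 243 participants. They are little changed by whether overall power is 75% or 80%. Discordant strata may be misread; the documents do not show that they will be. The change is worth making because it is nearly free, but the main conclusion of the study does not depend on it.

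**What to change.** In Statistical methods, state that for each stratifying variable the primary GEE model will be fitted in the full analysis set with a treatment-by-variable interaction. Report the interaction p-value together with stratum-specific effects and 95% CIs, label these analyses exploratory, and draw no claim from significance within a stratum. Add that a non-significant interaction will not be taken to show equal effects, given the low power. In Outcomes and Statistical methods, use one term for the hospital variable, defined as the variable used to stratify randomization. The cost is three interaction terms and a few sentences; no further data are needed.
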